**Methods/Design:**

CAPiTA is a placebo-controlled double-blind RCT evaluating the effectiveness of a 13-valent conjugated pneumococcal vaccine in preventing vaccine-type pneumococcal CAP in 84,496 elderly in the Netherlands. Participants of CAPiTA, who consented and provided information on health status (EQ-5D) and socio-demographic background at the time of vaccination, constitute the source population of CHO-CAP and are eligible for the nested matched cohort study. CHO-CAP patients hospitalized with CAP form the “diseased” cohort and the “non-diseased” cohort consists of unaffected persons (i.e. no CAP). Observations in the diseased cohort and in matched controls from the non-diseased cohort are used to determine excess costs and QoL changes attributable to CAP.

Based on an estimated 2,000 CAPiTA participants being hospitalized with CAP and an assumed CHO-CAP participation rate of 30% of all CAPiTA participants (±25,000), 600 CAP episodes are expected among CHO-CAP participants (the “diseased” cohort). For each patient with CAP, two non-diseased CHO-CAP subjects will be selected from the CHO-CAP cohort, with matching for age, gender and EQ-5D baseline-score. Data on healthcare and non-healthcare resources use, quality-of-life (using EQ-5D and SF-36 questionnaires) and selected health outcomes will be collected at 0, 1, 6 and 12 months after hospitalization for CAP.

The CHO-CAP study was approved by the Central Committee on Research involving Human Subjects in the Netherlands.

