The “Costs, Health status and Outcomes of CAP” study (CHO-CAP), in full “Collecting health outcomes and economic data on hospitalized Community-Acquired Pneumonia – a prospective cohort study”, is designed to prospectively determine health outcomes, quality-of-life (QoL) and costs associated with CAP for a period of 12 months after hospitalization due to CAP.

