#### Nested matched cohort study

As part of the CAPiTA trial, patients with a clinical suspicion of CAP are tracked in 56 Dutch sentinel hospitals. The duration of follow-up within CAPiTA is defined by the number of primary endpoints captured (i.e. 130 first CAP episodes caused by vaccine-type *S. pneumoniae* serotypes). It is expected that around 2,000 CAP episodes will occur within the study population [1]. Assuming a response rate of ~30%^a^ for the baseline questionnaire, we expected approximately 600 first CAP episodes among CHO-CAP participants. Local research nurses in sentinel hospitals notify the CHO-CAP team of newly admitted CAPiTA patients with a clinical suspicion of CAP directly after hospital admission and at the time of discharge. After discharge, eligible patients (i.e. CHO-CAP participants) will be asked to participate in the prospective cohort study for a period of one year. Patients are informed (orally and by written information) that participation involves one interview during a home visit, with three subsequent questionnaires to be completed during the 12 month period. Patients again provide informed consent upon inclusion in the prospective cohort study. Exclusion criteria for the prospective cohort study are hospitalization for a second (or further) hospitalization for CAP related complaints, inability to complete questionnaires, or a recent diagnosis of malignancy as the study was considered too burdensome for this latter group.

For each patient with CAP in the prospective cohort study (“diseased” cohort), two matched unaffected subjects (i.e. no CAP episode until the time of matching) will be selected from the baseline population for inclusion in the “non-diseased” cohort (see Figure 1). Matching is based on age (same age, with allowance of 3 years age difference), gender and baseline health status (same EQ-5D score [22], with maximum allowance of 5 percent points difference). Expectations are that both in the short-term and the medium term, CAP patients consume more medical resources, require more (in)formal help, might experience more trouble to get back to their daily activities, and have a lower quality-of-life than their non-diseased peers. Furthermore, mortality, both within-hospital as during the 12 months follow-up period, is expected to be higher in CAP patients than in controls.

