#### Nested matched cohort study

Each identified CHO-CAP participant hospitalized with CAP and interested in participation in the prospective “diseased” cohort is visited at home by a trained interviewer. Informed consent is obtained during this home visit. If consent is given, questions on health status, co-morbidities, current living situation and healthcare resources used before hospital admission are collected (see details in Table 2). A diary for own recording of healthcare resource use and other out-of-pocket expenses in the forthcoming period (i.e. one month) is explained and provided. Healthcare resources used during hospital admission (i.e. length of hospitalization, medication, diagnostics, interventions (e.g. surgery), complications, ICU admission) is collected from hospital databases by local trial nurses.

**Table 2 T2:** **Data collection in matched cohort-study**^
**a**
^

**Cohort**	**Diseased cohort (i.e. CAP patients)**** *During home visit; Contact at baseline* **	**Non-diseased cohort (i.e. unaffected (no CAP) persons)**** *During home visit; Contact at baseline* **	**Diseased/non-diseased cohort**** *Per post; Contact at 1, 6 and 12 months* **

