**Data collected:**			
*Demographic data*	➣ Current living situation	➣ Current living situation	➣ Current living situation
*Quality-of-life data*			
➣ 5-item EQ-5D instrument & VAS [22]	➣ As on day of interview	As on day of interview	As on day of interview
	➣ Referring back to worst moment of CAP episode		
	➣ Referring back to time previous to CAP episode		
➣ 36-item SF-36D instrument [24,25]	n.a.^b^	➣ 36-item SF-36D instrument [24,25]	➣ 36-item SF-36D instrument[24,25]
*Co-morbidities*			
➣ Stroke and/or cardio-vascular event	➣ Since participating in CAPiTA;	➣ Since participating in CAPiTA,	➣ Since last contact moment;
➣ 28-item standard list of major comorbid diseases developed by Statistics Netherlands	➣ 28-item standard list of major comorbid diseases	➣ 28-item standard list of major comorbid diseases	n.a.^b^
*Medical resources used:*			
➣ Medication used	➣ Previous to hospital admission to treat CAP;	n.a.^b^	➣ Since last contact moment;
➣ GP; emergency department and other medical specialist consultations (phone; office and home consultation(s))	➣ Previous to hospital admission to treat CAP;	n.a.^b^	➣ Since last contact moment;
➣ Outpatient visit(s) and treatment(s)	n.a.^b^	n.a.^b^	➣ Since last contact moment;
➣ Hospital admission(s) and treatment(s)	n.a.^b^	n.a.^b^	➣ Since last contact moment;
➣ Institutional care admission(s) others than hospital	n.a.^b^	n.a.^b^	➣ Since last contact moment;
*Home care*			
➣ Professional home care used	➣ Previous to hospital admission during the CAP episode?	In month previous to interview	➣ Since last contact moment;
*Productivity losses due to absence from patient/control from unpaid work (including replacement)*			
➣ Is unpaid work conducted on a regular base.	➣ Previous to CAP hospital admission	n.a.^b^	➣ Since last contact moment;
➣ Absent from unpaid work: For how long. Who took the work over?	➣ Previous to hospital admission during the CAP episode?	n.a.^b^	➣ Since last contact moment;
*Productivity losses due to absence of caregiver(s) from (un)paid work*			
➣ Informal home care used: By who? And for how long?	➣ Previous to hospital admission during the CAP episode	n.a.^b^	Since last contact moment;
*Travel costs:*			
Method of transport and cost	➣ To hospital when admitted with CAP	n.a.^b^	n.a.^b^
	➣ After discharge from hospital to home/nursing home	n.a.^b^	n.a.^b^
*Other cost/out-of-pocket expenses* (open question)	n.a.^b^	n.a.^b^	➣ Since last contact moment;

Note:

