a) Questionnaires (in Dutch) are available on request from first author.

b) n.a. = not applied.

Similar procedures are followed for the controls. An identified and eligible control who expressed interest to participate at the time of vaccination is visited at home. If consent is given, a questionnaire similar to that administered in the “diseased” cohort is provided (see details in Table 2).

In both the “diseased” and “non-diseased” cohorts, further data is collected on 1, 6 and 12 months after the initial home visit. Questionnaires are send by post, with the request to fill-in and send back within a week. If no response is received, participants are contacted by phone. This follow-up questionnaire addresses current living conditions, quality-of-life, co-morbidities and healthcare resources used (Table 2). A new diary for recording of healthcare use and other out-of-pocket expenses in the forthcoming period is provided once the questionnaire has been returned.

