## Discussion

The infrastructure of the CAPiTA trial offers a unique opportunity for prospective collection of health outcomes, QoL and cost data of patients hospitalized with CAP. Such data will facilitate the construction and validation of health economic models on cost-effectiveness and cost-utility of 13vPnC in the future, should this become necessary if vaccine efficacy and safety is demonstrated.

One of the limitations of the current study is that we might mainly reach the ‘healthier’ part of the community-dwelling CAPiTA participants, as older and more diseased subjects may be less willing to participate in additional research projects next to the main CAPITA trial. To gain insight into this possible bias, we will compare the baseline demographic data of the CHO-CAP cohort population with the larger CAPiTA population. Further, data gathered within the CAPiTA-study will enable us to compare CAP cases from the current CHO-CAP cohort with all CAP cases, for instance with regard to duration of hospitalization and occurrence of complications.

With an expected 600 CAP episodes we expect to constitute one of the biggest prospectively studied cohorts of hospitalized elderly with CAP with regard to resources use and QoL data. Strengths of this study further include collection of out-of-pocket costs of patients and productivity losses of both patients and their caregivers and the follow-up period of up to one year post-discharge. Our study is expected to add more in-depth knowledge on the short and longer term outcomes of pneumonia in elderly.

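### Follow-up is timed from the home visit in the methods but from hospitalisation or discharge elsewhere, and on the home-visit clock cases' resource use between discharge and visit goes almost entirely unrecorded

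*Protocol article*

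**What the plan says.** **The clock.** The abstract (Methods/Design) says that resource use, quality of life and outcomes "will be collected at 0, 1, 6 and 12 months after hospitalization for CAP". The Background describes the aim as determining these "for a period of 12 months after hospitalization due to CAP". Both the abstract's Discussion and the main Discussion name "the follow-up period of up to one year post-discharge" as a strength. The operational rule, under Data collection, Nested matched cohort study, is that in both cohorts "further data is collected on 1, 6 and 12 months after the initial home visit".

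**Enrolment.** Under Study design: "After discharge, eligible patients (i.e. CHO-CAP participants) will be asked to participate in the prospective cohort study for a period of one year". No limit is given for the time from discharge to the home visit.

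**Recall windows.** At the cases' home visit, "current living situation and healthcare resources used before hospital admission are collected". Table 2 gives the window for medication and consultations as "Previous to hospital admission to treat CAP". Professional home care, unpaid work and informal care are likewise asked about for the time before admission. Outpatient care, hospital admissions, institutional care and other out-of-pocket costs are marked as not applied at that visit. Use during the stay comes from hospital databases. The diary handed over at the visit runs forward, and the forms at 1, 6 and 12 months ask about the time since the previous contact.

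**The concern.** Two things follow if the text is applied as written.

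First, a contact labelled 1 month after hospitalisation takes place 1 month after a home visit that is itself some unstated and probably variable time after discharge.

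Second, and more important, use of care between discharge and the visit falls between two recall windows. Primary objective 2 is the difference in resource use over 12 months between elderly people with and without CAP. The protocol itself expects cases to use more medical care and more formal and informal help in the short term. Its Background criticises earlier studies for little or no follow-up after discharge and argues that all healthcare use should be counted. The uncovered interval is the start of that period. Only cases have it, because controls have no index discharge. The later forms cannot recover it, since each looks back only to the previous contact.

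**Working it through.** **Step 1: coverage for cases, window by window (Data collection text and Table 2).**

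| Window | Source | Resource items covered |
|---|---|---|
| Before admission | Home-visit interview | Medication, consultations, home care, unpaid work, informal care, travel to hospital |
| Admission | Hospital databases | Length of stay, medication, diagnostics, interventions, complications, ICU |
| Discharge to home visit | Home-visit interview | Journey home or to a nursing home only |
| After home visit | Diary; forms at 1, 6 and 12 months | All resource items except travel, since previous contact |

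At month 1 the previous contact is the home visit. The third window therefore has no item on medication, consultations, outpatient care, readmission, institutional care, home care, informal care, unpaid work or out-of-pocket costs.

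**Step 2: controls.** Their follow-up also starts at the home visit, but no index discharge precedes it, so there is no corresponding gap. Their home care is asked about for the month before the interview, whereas cases' home care is asked about only for before admission.

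**Step 3: size.** The article gives no discharge-to-visit interval *g* and no length of stay *L*, so it has no figure of its own to reproduce here. I assume *g* = 7, 14 or 28 days and *L* = 5 to 15 days, with a month of 30.4 days.

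- Share of the first 30 post-discharge days unrecorded: *g*/30.
- Length relative to a year: *g*/365.
- Day of a contact after discharge: 30.4 × months + *g*.
- Day of a contact after admission: the same plus *L*.

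| *g* (days, assumed) | *g*/30 | *g*/365 | 1-month contact, day after discharge | 12-month contact, day after discharge |
|---|---|---|---|---|
| 7 | 23% | 1.9% | 37 | 372 |
| 14 | 47% | 3.8% | 44 | 379 |
| 28 | 93% | 7.7% | 58 | 393 |

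Counted from admission, the 1-month contact falls between day 42 (30.4 + 7 + 5) and day 73 (30.4 + 28 + 15).

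**Step 4: quality of life.** Table 2 has EQ-5D and VAS on the day of the home visit in both cohorts, so an early EQ-5D contrast exists whatever the label. The SF-36 is not applied to cases at that visit. Their first SF-36 is the month-1 form, so the delay bears mainly on that instrument.

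**The case against.** **Summary wording.** The statements in the abstract and Discussion are summaries, and the methods give one explicit rule that is the same for both cohorts. After hospitalisation may simply mean after the stay, which would make it the discharge clock. That stands in part. A reader might infer three competing origins, but the text firmly supports only two. The home-visit clock differs from the others on either reading.

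**Condensed article.** The questionnaires are available separately, and their wording may be wider than the labels in Table 2. That is possible. But Table 2 is not silent: it states a window for each item, or marks it as not applied, and none of the windows for use of care reaches this interval. If the forms do cover it, Table 2 needs correcting.

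**Nothing at all recorded.** A reader might infer this, and it is too strong. The journey from hospital is recorded. The visit also takes current living situation and any stroke or cardiovascular event since joining CAPiTA, although these give status and events rather than resource use.

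**A second gap from the diaries.** The text says "A new diary for recording of healthcare use and other out-of-pocket expenses in the forthcoming period is provided once the questionnaire has been returned", and one might infer that late returners lose data. The documents do not support that. The next form asks about the whole time since the previous contact whether or not a diary was held, and non-responders are telephoned. Recall may suffer, but the period is covered.

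**Lost early quality of life.** One might infer that the early deficit is missed, or try to quantify how far the 1-month contrast shrinks. EQ-5D at the home visit answers the first. The documents give no recovery rate for the second.

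**Length of follow-up.** Each case still contributes 12 months after the visit, plus the admission. That is correct: the period is displaced rather than shortened, and what is lost is its first part.

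**Size.** Research nurses notify the team at discharge, so visits could be prompt and the gap short. That is fair; the interval is simply not stated.

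**Conclusion.** The point holds in this form. The home-visit clock conflicts with the timing given in the abstract, the aim and the discussions. On the home-visit clock, the stated recall windows omit cases' use of care from discharge to visit, apart from the journey from hospital. The omission affects cases only, so it tends to understate excess resource use and cost in primary objective 2. That direction rests on the protocol's own expectation of higher short-term use in cases.

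The size cannot be fixed from the article. For assumed intervals of 7, 14 and 28 days, 23%, 47% and 93% of the first 30 post-discharge days are unrecorded; shorter intervals give proportionally less. These are shares of time, not of cost. Contacts labelled by months after hospitalisation are late by the same interval if counted from discharge, and by the length of stay as well if counted from admission. For EQ-5D this is mostly a matter of labelling; for the SF-36 it affects the first measurement in cases.

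**What to change.** 1. State one time origin, use it in the abstract, Background, methods and Discussion, and apply it to the matched controls. If it is a date in the case's admission, assign that date to the case's controls and let their resource questions reach back to it as well. If it is the home visit, say so throughout and add the discharge-to-visit use of cases as a separate component.
2. Add a since-discharge block to the cases' home-visit interview, with the resource items of the follow-up form. For cases already visited but not yet at month 1, let that form ask about the time since discharge.
3. Record the discharge and visit dates, report the distribution of the interval, and analyse or report quality of life and costs by actual days since the origin.

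The cost is a slightly longer interview that is already being held, a changed recall period on one form, two dates per case, and aligned wording. For cases past month 1 this route does not recover the interval; its length should be reported as a limitation.

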### Objective

CHO-CAP comprises the collection of cost data and quality-of-life data in elderly with and without CAP. The primary objectives are:

1. To determine, during a 12 month follow-up period, differences in quality-of-life of elderly with and without CAP.

2. To determine, during a 12 month follow-up period, differences in resource use (healthcare and non-healthcare) in elderly with and without CAP.

The secondary objective is to describe the baseline health status and quality-of-life of a community-dwelling elderly population eligible for participation in the CAPiTA study.

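### Issuing each new diary only after the previous questionnaire is returned leaves non-returners with no diary for the next 5 or 6 months of the resource-use follow-up

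*Protocol article*

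**What the plan says.** The relevant text is in the protocol article, Data collection, under Nested matched cohort study.

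- **First diary.** At the home visit: "A diary for own recording of healthcare resource use and other out-of-pocket expenses in the forthcoming period (i.e. one month) is explained and provided". This is described for the patients with CAP; the article says that controls follow similar procedures.
- **Follow-up rounds, both cohorts.** The timing is given as: "further data is collected on 1, 6 and 12 months after the initial home visit". The forms are mailed, and participants have one week to return them. For a form that does not arrive, the article says only this: "If no response is received, participants are contacted by phone".
- **Later diaries.** The rule for the next diary is: "A new diary for recording of healthcare use and other out-of-pocket expenses in the forthcoming period is provided once the questionnaire has been returned". The article does not say what happens to the diary when a form is never returned.
- **What the forms ask.** In Table 2, nearly all resource items on the postal forms, and the open question on out-of-pocket cost, carry the window "Since last contact moment".
- **What depends on it.** The second primary objective reads: "To determine, during a 12 month follow-up period, differences in resource use (healthcare and non-healthcare) in elderly with and without CAP".

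**The concern.** A diary helps only if it is in the participant's hands while the use occurs. Here it is tied to an administrative event, the return of a form, and that event can fall only after the previous diary's period has ended. The tie is weakest in practice for participants who respond least, and they lose the aid for longest.

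Hospital databases are named only for the CAP admission itself. Use after the home visit, and all out-of-pocket spending, comes from what participants report on the postal forms. The Discussion lists out-of-pocket costs and productivity losses as strengths of the study, and these are items for which memory over several months is a poor substitute for notes.

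The effect on the cost difference can be stated conditionally. Let D be the true difference in mean use between cohorts. If the same fraction f of use is forgotten in both, the observed difference is (1 − f) × D, so excess use is understated even when recall is equally poor in the two groups. If the fractions differ between cohorts, the direction is not fixed.

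**Working it through.** **The plan's own figures.** The article gives no figure for diary coverage. Its only planning numbers reproduce (2,000 × 0.30 = 600 cases; 600 × 2 = 1,200 controls) and do not enter this check.

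**Inputs from Data collection, Nested matched cohort study.** The first diary lasts 1 month. Forms are due at months 1, 6 and 12, so the windows are 1, 5 and 6 months. Return is asked within 7 days. The next diary depends on return.

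**Conventions and assumptions.** One month = 365.25 / 12 = 30.44 days, so 5 months = 152.2 days and 6 months = 182.6 days. Only the 7-day lag has a basis in the article; lags of 14, 28 and 56 days are assumptions that show the range.

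**Formula.** Days without a diary = g1 + g6. Here g1 is the return lag of the month-1 form (152.2 if never returned) and g6 the lag of the month-6 form (182.6 if never returned). Coverage = 1 − (g1 + g6) / 365.25.

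| Month-1 form back after | Month-6 form back after | Days without a diary | Share of 12 months covered |
|---|---|---|---|
| 7 days | 7 days | 14 | 96.2% |
| 14 days | 14 days | 28 | 92.3% |
| 28 days | 28 days | 56 | 84.7% |
| 56 days | 56 days | 112 | 69.3% |
| never | 0 days | 152.2 (5.0 months) | 58.3% |
| 0 days | never | 182.6 (6.0 months) | 50.0% |
| never | 7 days | 159.2 (5.2 months) | 56.4% |
| 7 days | never | 189.6 (6.2 months) | 48.1% |
| never | never | 334.8 (11.0 months) | 8.3% |

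**Two limits on these counts.** The new diary's time in the post is left out, which makes the lag rows too small. The first diary is taken to stop on the scheduled date. A participant who keeps writing in it until the form is completed has a shorter gap, which makes the lag rows too large. Neither materially changes the rows with a form never returned.

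**Cohort level.** If proportions p1 and p6 never return the month-1 and month-6 forms, the average share of diary time lost, apart from lags, is (5 × p1 + 6 × p6) / 12. Each percentage point of non-return at both rounds therefore costs 11/12 = 0.92 of a percentage point. The article gives neither p1 nor p6, so the expression cannot be evaluated.

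**What happens to the data.** Take the window on the next form to start at the last completed form. After a missed month-1 form, the month-6 form covers months 0 to 6, with diary notes for the first month only. After a missed month-6 form, the month-12 form covers months 1 to 12, an 11-month window whose last 6 months have no diary. The period is still asked about in both cases; what is lost is the aid.

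**With diaries issued on schedule**, g1 = g6 = 0 and the gap caused by the return condition is 0 of 12 months.

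**The case against.** The best defence is that the diary is an aid and the questionnaire is the dataset. Table 2 lists the resource and out-of-pocket items as asked on the forms, and no separate diary-based outcome is named. Use during the CAP admission comes from hospital records and is untouched. The one-week request and the telephone contact limit lateness, and sending a diary only after a return confirms that the participant is still in follow-up, which matters where deaths are expected. All of this stands. It limits the consequence to longer unaided recall, but it does not remove the 5 or 6 months without a diary after a form that never comes back.

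The documents do not support several stronger readings that a reader might infer:

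- **Late forms cost months of diary.** They cost days or weeks; even 56 days late at both rounds gives 3.7 months in all. Only a form never returned costs 5 or 6 months by itself.
- **Use is double counted or dropped because the windows shift.** This does not follow from the text. If the window starts at the last completed form, the windows are contiguous. If it started at the scheduled date, a form completed 7 to 28 days late could repeat 4.6% to 18.4% of the 5-month window (7/152.2 and 28/152.2), and a missed month-1 form could drop the first month. The article does not say which start applies, and the Dutch questionnaires, offered on request, may settle it. Table 2's column headings use the word contact for the baseline visit and the scheduled rounds, which speaks against treating a reminder call as the start of a window.
- **The affected participants are sicker, are more often cases, or lose their costliest month.** The Discussion expects older and more diseased people to be less willing to join, but says nothing about who returns forms. No costs by month are given, and the follow-up procedure is the same in both cohorts.

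**Conclusion.** The point holds in a limited form. By the article's own rule, an on-time responder has a short interval without a diary at the start of each later window (14 days over the year if both forms are back in 7 days, before postage). A participant who never returns the month-1 or month-6 form has no diary for the following 5 or 6 months, or 11 of 12 months if both are missed. For these people the second primary objective rests on unaided recall.

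This assumes that the rule is applied as written, with no diary sent after an unsuccessful telephone contact. The number affected and the resulting bias in excess cost cannot be derived from the article. It is a cheap improvement to data quality, not a defect that invalidates the comparison.

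**What to change.** Separate the diary from the return of the form. Either hand over all diaries at the home visit, each labelled with its period, or mail each diary on its scheduled date together with the questionnaire, whether or not the previous form came back.

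At the same time, print a start and an end date on every diary and form. A diary handed over in advance can carry the scheduled dates. The start date on a form should be the end date of the last form actually returned, so that a missed form lengthens the window and does not drop a period.

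The cost is small: the same diaries, pre-printed dates and no additional mailing. The downsides are some unused diaries for participants who die or withdraw, and a short time with two diaries in hand. The period labels are there to limit split or duplicate entries during that time.
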